#### Secondary outcomes

Secondary outcomes with details on the statistical analyses are summarized in Table 1.

**Table 1 Tab1:** Summary of the secondary objectives with the statistical analysis and time of measurement

	**Secondary outcomes**	**Details of statistical analysis**^**a**^	**Time of measurement**
**Short-term mortality and comorbidity**	- Bronchopulmonary dysplasia (NICHD criteria) - Death	Logistic regressions will be performed, corrected for GA and centre, for BPD and death separately, and the combined outcome of BPD and death. Survival analysis will be performed for time to death. Cause-specific risk models will be computed to consider death as competing risk for severe disabilities at 18 to 24 months of age.	Postmenstrual age of 36 weeks and hospital discharge
	**Admission:** - Length of stay intensive care - Length of stay hospital	Survival analyses will be performed for time to discharge.	Hospital discharge
	**Respiration:** - Incidence of endotracheal intubations - Number of days on invasive ventilation - Number of days on respiratory support - Number of days with supplemental oxygen - Respiratory complications - Use of postnatal corticosteroids	Logistic regression analysis will be performed for the dichotomous respiratory complications and the use of corticosteroids. Linear regression analysis will be performed for the incidence of endotracheal intubations, and number of days on invasive ventilation, respiratory support, and supplemental oxygen. In both analyses will be corrected for GA and centre. A survival analysis will be performed for the time to intubation.	Hospital discharge
	**Gastro-intestinal:** - Solitary intestinal perforation - Necrotizing enterocolitis > stage 2 (Bell’s criteria) - Feeding problems (days with parental feeding after inclusion) - Body weight - Head circumference	Logistic regression analysis will be performed for SIP, NEC and feeding problems. Linear regression analysis will be performed for body weight and head circumference. Both analyses will be corrected for GA and centre.	Hospital discharge
	**Neurological:** - Intravenous haemorrhage - Clinical seizures - Periventricular leukomalacia	Logistic regression analysis will be performed for all neurological outcomes, corrected for GA and centre.	Hospital discharge

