	**Complications:** - Incidence of late-onset sepsis - Meningitis after inclusion - Need for inotropes/ respiratory support	Logistic regression analysis will be performed for all complications, corrected for GA and centre.	Hospital discharge
	- Retinopathy of prematurity	Logistic regression analysis, corrected for GA and centre, will be performed for retinopathy ‘yes’ or ‘no’.	Hospital discharge
	- Hearing loss	Logistic regression analysis, corrected for GA and centre, will be performed for hearing loss ‘yes’ or ‘no’.	Hospital discharge
**Long-term outcomes**	- Readmission since first hospital discharge - Body weight - Body length - Head circumference - Behavioural problems (Child Behavior Checklist) - Cognitive and language development	Logistic regression analysis will be performed for readmissions, behavioural problems, and cognitive and language problems. Linear regression analysis will be performed for body weight, body length, and head circumference. In both analysis will be corrected for GA and centre. Survival analysis will be performed for the time to readmission.	Eighteen to 24 months of corrected age
**Cost-effectiveness**	- (Non-)medical costs during and after hospital admission - Patient outcomes; survival, severe disability, and health-related quality of life (HRQoL)	The total costs per patient and quality-adjusted life years (QALYs) will be assessed. Incremental cost-effectiveness ratios (ICERs) will be calculated, expressed as incremental costs per additional survivor without severe disability at 2 years and incremental costs per QALY gained.	Eighteen to 24 months of corrected age
**Pharmacokinetics**	- Blood samples	Exposure of (keto-) doxapram will be calculated from an existing PK model. The cumulative exposures will be calculated and analysed using a linear regression model, corrected for centre.	During level 3 NICU admission
**Respiratory effects**	- Vital sign data (oxygen saturation, respiratory rate, heart rate, blood pressure) - Ventilation data (ventilation mode, fraction of inspired oxygen, flow)	Vital sign data will be analysed as continuous data. Logistic regression analysis will be performed for all vital sign data, corrected for GA en centre. Mixed model analysis will be performed to take into account repeated measurements. Ventilation duration and cumulative inspired oxygen need and flow will compared using the *t*-test or Mann-Whitney test.	During level 3 NICU admission

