### Secondary short-term outcomes

Secondary outcomes include the respiratory condition of the patient (BPD (NIH 2001 definition [6]), number of days on invasive ventilation, incidence of endotracheal intubation), death (before a postmenstrual age of 36 weeks), duration of NICU and hospital admission, use of postnatal corticosteroids, body weight (at 36 weeks and hospital discharge), solitary intestinal perforation or NEC > stage 2 according to Bell, clinical seizures, intravenous haemorrhage, incidence of late-onset sepsis, meningitis, need for inotropes, retinopathy of prematurity, and an abnormal hearing test at term equivalent age.

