### Secondary long-term outcomes

Additional long-term outcomes at 18 to 24 months corrected age will be hospital readmissions, weight, length and head circumference and behavioural problems according to the Child Behavior Checklist [33]. The cognitive and language development will be assessed by the parent-reported PARCA-R questionnaire [34].

Moreover, we will carry out an analysis of cost-effectiveness, including an analysis of health-related quality of life (HRQoL). The potential health and economic gains of doxapram could be substantial due to the low price of doxapram (off-patent) and because it is expected to result in both shorter duration of ventilation, a decrease in length of hospital stay, improved life-long neurological development and less long-term medical needs. We will explore the plausibility of this hypothesis by performing a cost-utility analysis alongside the trial.

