#### Sample size calculation

The sample size calculation is based on a cohort study that investigated the long-term neurodevelopmental outcome of preterm infants who received doxapram therapy compared to non-treated matched control patients [20]. This paper described that 30% of the doxapram-treated patients had the composite outcome death or neurodevelopmental delay at 2 years corrected age compared to 50.8% in the non-treated control patients. We therefore consider an absolute decrease of 15% in the composite outcome as clinically relevant, and we aim to reduce the outcome from 50 to 35% with a number needed to treat of around 7 patients. With an alpha of 0.05 and a power over 80%, a sample size of 170 patients is needed per treatment arm when we use a continuity correction. Because we expect approximately 10 patients to be part of twins and a loss to follow-up rate (excluding death) of 10% per treatment arm, the sample size is 198 patients per treatment arm, adding up to a total of 396 patients to be included. Next to the formal consent letter, an animation and flyer are designed providing additional study information to optimize consent and to reach the targeted sample size.

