#### Randomization and blinding

Participants will be randomly allocated in a 1:1 ratio, stratified according to study centre and gestational age (<26 weeks or ≥26 weeks), and using random permutated blocks. Multiple birth infants will be randomized independently, unless parents or legal representatives explicitly request that siblings are to be allocated to the same treatment arm. Randomization and drug supply management is performed via an electronic online platform (ALEA®, FormsVision BV, Abcoude, the Netherlands).

Once the participant has been randomized, a study medication kit will be allocated. All treatment kits will be visually identical and contain either doxapram or placebo. The clinical trial centre and trial pharmacy of the Erasmus Medical Centre will manage the randomization list. The parents, researchers and medical team will have no access to the randomization list. Unblinding is only performed by an independent safety officer in emergency situations where knowledge of the study drug is considered absolutely necessary for the clinical management of the included patient.

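### Short-term weight and head circumference are compared at hospital discharge, a time treatment may shift, with no adjustment for age at measurement

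*Protocol article*

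**What the plan says.** Body weight and head circumference stand in the gastro-intestinal row of Table 1 (Secondary outcomes). The model is fixed there: "Linear regression analysis will be performed for body weight and head circumference. Both analyses will be corrected for GA and centre". The time-of-measurement column for that row names hospital discharge and nothing else.

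The GA covariate is a baseline factor. Eligibility is defined on GA at birth, and randomisation is "stratified according to study centre and gestational age (<26 weeks or ≥26 weeks". Neither postmenstrual age at measurement nor an age-standardised score is mentioned. The note under Table 1 adds unadjusted two-group tests for continuous secondary outcomes.

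Three other statements bear on this:

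- The admission row of Table 1 treats discharge time as an outcome: "Survival analyses will be performed for time to discharge".
- Secondary long-term outcomes says of doxapram that "it is expected to result in both shorter duration of ventilation, a decrease in length of hospital stay".
- Secondary short-term outcomes lists "body weight (at 36 weeks and hospital discharge"), so weight has a fixed-age time point that the growth row of Table 1 lacks. That paragraph does not list head circumference.

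Growth is compared again at 18 to 24 months corrected age: "Linear regression analysis will be performed for body weight, body length, and head circumference".

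**The concern.** Preterm infants gain weight and head size daily, so a raw measurement depends on the age at which it is taken. If one arm goes home earlier, its infants are younger when measured and will be lighter with smaller heads even if growth is identical. Adjusting for GA at birth does not help, because two infants born at the same GA can be discharged at different postmenstrual ages, and treatment may act on exactly that difference.

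The distortion works against the drug when the stay is shortened, which is what the protocol hopes for, and in its favour when the stay is lengthened. The Background and Discussion raise concerns about cerebral effects, so an apparently smaller head at discharge could be taken as a sign of harm. Conversely, a longer stay could conceal a real deficit.

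**Working it through.** **Plan's own figure.** None. The protocol gives no growth rate, SD or expected change in length of stay, so the calculation below only illustrates the size of the effect.

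**Inputs from the protocol.** 198 infants per arm; p<0.05, taken as two-sided.

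**Assumptions.** About 10% without a discharge measurement, so 198 × 0.9 = 178 per arm. Weight gain 20-30 g/day, weight SD 400-700 g. Head growth 0.5-0.8 cm/week, head circumference SD 1.5-2.0 cm. Discharge 3, 7 or 14 days earlier with doxapram. No true effect on growth.

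**Formulas.**

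- False deficit = days earlier × growth per day.
- SE = SD × √(2/178) = 0.106 × SD. This is 42.4 g (SD 400) to 74.2 g (SD 700), or 0.159 cm (SD 1.5) to 0.212 cm (SD 2.0).
- Chance of p<0.05 = Φ(deficit/SE − 1.96) + Φ(−deficit/SE − 1.96).

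**Worked cases for weight.**

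- 3 days, low end: 3 × 20 = 60 g; 60/74.2 = 0.81; Φ(−1.15) + Φ(−2.77) = 0.13.
- 3 days, high end: 3 × 30 = 90 g; 90/42.4 = 2.12; Φ(0.16) = 0.57.
- 7 days, low end: 7 × 20 = 140 g; 140/74.2 = 1.89; Φ(−0.07) = 0.47.
- 7 days, high end: 7 × 30 = 210 g; 210/42.4 = 4.95; Φ(2.99) > 0.99.

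| Discharge earlier by | False weight deficit | Chance of p<0.05 | False head deficit | Chance of p<0.05 |
|---|---|---|---|---|
| 3 days | 60-90 g | 13-57% | 0.21-0.34 cm | 17-58% |
| 7 days | 140-210 g | 47% to >99% | 0.5-0.8 cm | 66% to >99% |
| 14 days | 280-420 g | 97% to >99% | 1.0-1.6 cm | >99% |

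**Check on the regression form.** A simulation fitted linear regression on arm and GA at birth with robust standard errors (178 per arm, 25 g/day, 1,000 trials per setting, no growth effect). Centre was left out for simplicity.

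| Discharge earlier by | Mean difference at discharge | Significant at discharge | Mean difference at 36 weeks | Significant at 36 weeks |
|---|---|---|---|---|
| 0 days | −1 g | 5% | 0 g | 5% |
| 3 days | −78 g | 32% | −1 g | 4% |
| 7 days | −172 g | 91% | 2 g | 5% |
| 14 days | −350 g | 100% | −1 g | 6% |

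The discharge differences match days × 25 g (75, 175 and 350 g), so adjusting for GA at birth removes none of the bias. At a fixed 36 weeks the false-positive rate stays near 5%. With no shift in discharge there is no bias at either time.

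**The case against.** A reader might infer that a working drug is bound to look harmful to growth. The documents do not support that. The shorter stay is stated without a number, as part of the economic rationale, and the protocol says its plausibility is still to be explored. A shift of 3 days or less would often pass unnoticed. A true growth benefit, or discharge decisions guided partly by weight, would shrink or reverse the apparent deficit. This stands: the right word is could.

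A reader might also infer that no sound short-term growth comparison is planned. For weight that is wrong, because the text lists 36 weeks, and Table 1 is offered as a summary. For head circumference the text shown names no fixed short-term age, but the schedule of assessments (Fig. 2) is not shown, so its absence from the trial cannot be asserted.

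Extending the criticism to the 18 to 24 month measurements fails. That window is set on corrected age and is the same in both arms, and nothing suggests treatment moves the visit. Leaving age at that visit unadjusted costs precision but does not create a difference. Likewise, omitting sex does not bias a randomised comparison.

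The scale of the outcome (raw values or standardised scores) could be settled in an analysis plan not shown. But the article itself states outcome, model, covariates and time, and that combination names no correction for age at measurement. Finally, time to discharge will be reported alongside, so an attentive reader could see a difference in stay. That limits misreading but does not correct the estimate.

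**Conclusion.** The point holds in a limited form. As stated in Table 1, the discharge comparison of weight and head circumference is made at a time that treatment may change, and its covariates do not correct for that. The result could show a growth deficit that is only a difference in age, or hide a real one.

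The size depends on a discharge shift that the documents do not quantify. Under the stated assumptions the risk of a false finding is modest to moderate at 3 days and substantial at 7 days or more. These chances also rest on the assumed SDs, growth rates and 178 infants measured per arm; infants who die before discharge contribute no discharge measurement. The calculation treats the values as raw, which is how Table 1 reads but is not said outright.

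The weakness matters most for head circumference. For weight, the main defect is that Table 1 leaves out the 36-week time point the text already plans. The primary outcome, the sample size and the mortality stopping rule are untouched.

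**What to change.** 1. Add 36 weeks postmenstrual age to the growth row of Table 1, in line with Secondary short-term outcomes, and make it the main short-term comparison for weight. Do the same for head circumference where it is measured at that age.
2. Analyse discharge weight and head circumference as z-scores standardised for sex and postmenstrual age at measurement. Present raw discharge values as descriptive only, without a between-arm test.
3. Optionally, use age- and sex-standardised scores at 18 to 24 months as well. This would gain precision; it is not needed to remove bias.

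The cost is a change of analysis wording, best made before unblinding. Sex is already used in the planned adjusted analysis, and the discharge date is needed for time to discharge, so postmenstrual age at discharge can be derived. Two things should be confirmed: that discharge measurements were taken at or near the discharge date, and whether head circumference is recorded at 36 weeks. If it is not, the discharge z-score becomes its short-term analysis.

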### Pharmacological intervention

Participants will be randomized to receive either doxapram (as hydrochloride, 2 mg/ml in dextrose 5%, 50 mL) or placebo (dextrose 5%, 50 mL). Study medication is manufactured in ready to use 50-mL polypropylene vials and labelled by *Apotheek A15* in Gorinchem, the Netherlands, according to Good Clinical Practice and Good Manufacturing Practice guidelines. Doxapram and placebo fluids are visually identical as well as the labels and the vials, and the syringes in which the study medication will be prepared for blinded administration. Central stock of study medication is stored in the trial pharmacy of Erasmus MC in Rotterdam and dispensed to participating hospitals to supply the local stock.

Therapy is started with a loading dose of 2.0 to 2.5 mg/kg administered intravenously in 10 min, followed by a continuous maintenance dose of 0.5 to 1.0 mg/kg/h via intravenous infusion [17, 24]. The maintenance dosage can be titrated based on the clinical response of the patient; an increase of 0.5 mg/kg/h is recommended after 30–60 min in case of an insufficient effect of the study medication. Increases are allowed up to 2.0 mg/kg/h. If the study medication is effective, clinicians are encouraged to assess the possibility of step-by-step dose reduction of 0.5 mg/kg/h every 12–24 h. Dosage adjustments can also be made if side effects are suspected. Using the same formulation, a switch to gastro-intestinal administration via the nasogastric tube is feasible and allowed [25]. Gastro-enteral administration can be either continuous or intermittently from 4 times daily up to 24 times per day. Oral administration of the study medication requires a 33% higher dose, with a maximum dose of 2.0 mg/kg/h, compared to intravenous administration, due to the oral bioavailability of doxapram (74%) in preterm neonates [26].

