Additionally, the effect of doxapram on the primary outcome will be adjusted for important risk factors for neurodevelopmental impairment, based on the literature and our clinical experience. A multivariate logistic regression model will be computed including the independent variables small for gestational age, sex, and intraventricular haemorrhage in addition to the stratification variables [5, 37, 38]. A complete case analysis will be conducted if less than 10% of the randomized patients has missing data. In case of a higher rate of missing data, multiple imputation with sensitivity analyses will be conducted.

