### Secondary outcome analyses

Logistic and linear regression analyses will be performed for dichotomous and continuous secondary outcomes, respectively. Regression analyses will be adjusted for GA and admitted centre. Survival analyses using Cox proportional hazards regression will be performed to investigate the relations between the outcomes time to intubation, time to discharge, and time to death. Cause-specific risk models will be computed to consider death as competing risk for severe disabilities. This is done by estimating cumulative incidence functions using the Fine and Grey model [39].

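### The linear models for weight, length and head circumference adjust only for GA and centre, giving up precision that birth weight, already needed for the SGA covariate, could supply

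*Protocol article*

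**What the plan says.** Table 1 of the protocol article (Secondary outcomes) has a column for the details of the analysis. In its gastro-intestinal row, timed at hospital discharge, it says: "Linear regression analysis will be performed for body weight and head circumference. Both analyses will be corrected for GA and centre". In its long-term row, timed at 18 to 24 months corrected age, it says: "Linear regression analysis will be performed for body weight, body length, and head circumference. In both analysis will be corrected for GA and centre". The section Secondary outcome analyses sets the same rule for all secondary regressions: "Regression analyses will be adjusted for GA and admitted centre".

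The weight outcome is attained weight, not change: Secondary short-term outcomes lists "body weight (at 36 weeks and hospital discharge" as its two time points.

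Starting size appears elsewhere in the article. The additional model for the primary outcome is described as "including the independent variables small for gestational age, sex, and intraventricular haemorrhage in addition to the stratification variables", and SGA status cannot be assigned without birth weight. Study drug is also dosed by weight: "Therapy is started with a loading dose of 2.0 to 2.5 mg/kg administered intravenously in 10 min". The footnote to Table 1 specifies sandwich standard errors for the linear models.

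**The concern.** In a linear model of attained size, the residual contains whatever size differences existed before randomisation and are not explained by GA and centre. Birth weight is an obvious predictor of later size within a GA group, and it is measured before allocation, so adjusting for it cannot be distorted by treatment. Leaving it out widens the interval for the treatment effect. It also means that a chance difference between arms in starting size is not corrected in the estimate.

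The covariate set is stated outright in two rows of Table 1 and repeated as a general rule. It is therefore a choice that the article fixes, not a detail left to an analysis plan. At stake is how sharply the trial can estimate an effect of doxapram on weight, length and head circumference. The primary analysis and the sample size are not affected.

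**Working it through.** **Inputs from the article.** Covariates: GA and centre (Table 1; Secondary outcome analyses). Allocation: "Participants will be randomly allocated in a 1:1 ratio, stratified according to study centre and gestational age (<26 weeks or ≥26 weeks". Sample size: "With an alpha of 0.05 and a power over 80%, a sample size of 170 patients is needed per treatment arm", raised to 198 per arm for twins and 10% loss to follow-up.

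**Input assumed.** r is the partial correlation of birth weight with the outcome, given GA and centre. The article gives none, so a range is used: 0.3 to 0.7 for short-term outcomes and 0.2 to 0.4 at 18 to 24 months.

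**The plan's own figure.** The article states no power or precision for the growth outcomes, so there is no such figure to reproduce. The number per arm follows as (170 + 10) × 1.10 = 198. (The 170 for 50% versus 35% comes from the formula without continuity correction; with the correction that the article names, it is 183. That is a separate matter and does not bear on this point.)

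**Precision.** Adding the covariate multiplies the residual variance by 1 − r² and the interval width by √(1 − r²). The equivalent number per arm is 198 / (1 − r²).

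| r | Variance factor | Interval narrower by | Equivalent n per arm |
|---|---|---|---|
| 0.2 | 0.96 | 2.0% | 206 |
| 0.3 | 0.91 | 4.6% | 218 |
| 0.4 | 0.84 | 8.3% | 236 |
| 0.5 | 0.75 | 13.4% | 264 |
| 0.7 | 0.51 | 28.6% | 388 |

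**Power.** At 198 per arm, the effect detectable with 80% power and two-sided alpha 0.05 (two-sided assumed) without the covariate is (1.960 + 0.842) × √(2/198) = 0.28 residual SD. With the covariate, power for that same effect is 83.6% at r = 0.3, 89.9% at r = 0.5 and 97.5% at r = 0.7.

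**Chance imbalance.** The standard error of a baseline mean difference is √(2/198) = 0.10 SD, so a difference of 0.2 SD or more in either direction arises in about 1 trial in 20. It moves the estimate without birth weight by r × 0.2: 0.06 SD at r = 0.3 and 0.14 SD at r = 0.7. The adjusted model removes that shift.

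**Check by simulation.** Linear regression with sandwich (HC3) standard errors, 396 infants, 1,000 runs per setting and no treatment effect: the standard error fell by 4.3%, 13.1% and 28.5% at r = 0.3, 0.5 and 0.7. Coverage was 94 to 96% both with and without the covariate. Because r was an input, this confirms the formula and the validity of both models, not the size of the gain in this trial.

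All figures use 198 per arm. Death and loss to follow-up will reduce that number, but the proportional narrowing does not depend on it.

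**The case against.** The strongest case on the other side is that nothing here is an error. Adjusting every secondary regression for the two stratification factors is a uniform and valid rule, and adding a prognostic covariate for a few of many secondary outcomes could be called preference. That stands as a limit on severity: this is an efficiency point only. It does not remove the point, because the rule is fixed in the article and the better covariate appears to be at hand.

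The size of the gain is also open to challenge. Each infant is discharged at a different age, and length of stay is itself an outcome. If smaller infants stay longer, weight at discharge may correlate only weakly with birth weight. A higher correlation is more plausible at 36 weeks. This objection stands, and it is why a correlation as high as 0.8 is not used.

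Three stronger readings are tempting, and the article does not support them:

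- A reader might infer that infants who were small before randomisation are counted as a drug effect, so that the planned comparison is biased. Randomisation rules this out on average, and the standard error of the planned model already allows for chance imbalance.
- A reader might infer that weight and head circumference are the plan's designated measures of nutritional or brain-growth harm. The article lists them under gastro-intestinal and long-term outcomes. It follows safety through adverse drug reactions, clinical complications and the primary composite.
- A reader might infer from dosing per kg that weight at randomisation is in the database. Dosing shows that a weight is known at the bedside, not that it is recorded as trial data. Likewise, nothing shown says that baseline head circumference is recorded. Only birth weight is reasonably implied, through SGA.

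**Conclusion.** The point holds as a modest, low-cost improvement. The growth models are fixed as adjusted for GA and centre only, while the article's own SGA covariate implies that birth weight is available. The planned comparison is unbiased with correct coverage. The loss is precision and protection against chance imbalance in starting size.

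The size rests wholly on an assumed correlation. The interval would be about 5 to 29% narrower for short-term outcomes (r = 0.3 to 0.7) and about 2 to 8% narrower at 18 to 24 months (r = 0.2 to 0.4), with the gain at discharge possibly below the short-term range. For head circumference and length, birth weight is a proxy for the corresponding baseline measurement, so the lower part of the range may be the safer expectation there. The article does not say whether GA enters the Table 1 models as a continuous variable or as the two randomisation strata. If it enters as strata, more variation in size is left for birth weight to explain.

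**What to change.** In both Table 1 rows, and in the general rule for secondary regressions as it applies to growth, prespecify birth weight as one continuous covariate in every linear model of body weight, body length and head circumference. Keep GA, centre and the planned robust standard errors. Name this single variable and do not leave a choice between birth weight and weight at randomisation.

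For head circumference, baseline head circumference may replace or be added to birth weight only if it is recorded for all infants. The two variables should not be mixed across infants within one covariate.

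The cost is one covariate in the analysis plan, set before unblinding so that it cannot look data-driven. No new data should be needed, provided the sponsor confirms that the database holds birth weight itself and not only the SGA classification. The primary analysis and the sample size stay as they are.

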#### Interim analysis and stopping rules

After inclusion of 80 (20%), 200 (50%) and 300 (75%) patients, an interim analysis will be performed to protect the safety, validity and credibility of the trial. There will be no stopping rules for futility. Patient inclusion will be stopped, however, if neonatal mortality is at least 10% higher (absolute difference) in either the placebo arm or the doxapram arm, and if this difference is statistically significant. A difference is assumed statistically significant if a two-sided *p*-value is less than 0.05, based on Fisher’s exact test. The confidence interval for the risk difference will be based on the method of Newcombe [35]. These analyses will not be adjusted for covariates. A reduced set of baseline variables, including at least gestational age and sex, and outcomes, including at least death, BPD and the composite outcome death or severe disability (where already available), will also be studied at the time of the interim analysis.

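### Growth at 18–24 months is adjusted for GA and centre only; sex, already collected, and age at the visit could be taken out of the error term at almost no cost

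*Protocol article*

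**What the plan says.** Protocol article, Secondary outcomes, Table 1 (Long-term outcomes): "Linear regression analysis will be performed for body weight, body length, and head circumference". The same cell sets the covariates: "In both analysis will be corrected for GA and centre". The section Secondary outcome analyses repeats the rule for all secondary regressions: "Regression analyses will be adjusted for GA and admitted centre".

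The section Secondary long-term outcomes lists the measures without a scale: "Additional long-term outcomes at 18 to 24 months corrected age will be hospital readmissions, weight, length and head circumference". No standardised score or growth reference is named.

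Three other places bear on sex:

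- Randomization and blinding: allocation is "stratified according to study centre and gestational age", so sex is not balanced by design.
- Interim analysis and stopping rules: "A reduced set of baseline variables, including at least gestational age and sex" will be examined, so sex is collected at baseline.
- Primary outcome analyses: the additional model for the primary outcome is fitted "including the independent variables small for gestational age, sex, and intraventricular haemorrhage in addition to the stratification variables". Sex is thus treated as a relevant risk factor there.

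**The concern.** Sex and age are obvious predictors of a toddler's weight, length and head circumference. As the model stands, sex variation is removed neither by stratification nor by a covariate. Variation from age within the six-month window is removed only as far as each centre sees its children at one fixed age, in which case the centre term absorbs it.

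The stake is precision and nothing else. In a randomised comparison analysed by linear regression, leaving out a prognostic baseline variable does not bias the treatment estimate. The sandwich standard errors that the plan specifies keep the inference valid, but they do not recover the lost precision. The comparison among survivors who attend follow-up is a separate question and is not raised here.

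**Working it through.** **Figure to reproduce.** There is none: the plan powers no secondary outcome and gives no SD or expected difference for growth. All growth inputs below are therefore assumptions, given as ranges.

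| Input (assumed) | Weight | Length | Head circumference |
|---|---|---|---|
| Boy–girl difference d | 0.5–0.7 kg | 1.0–1.6 cm | 0.9–1.2 cm |
| SD within age and sex | 1.1–1.4 kg | 3.0–3.5 cm | 1.3–1.6 cm |
| Growth per month r | 0.15–0.25 kg | 0.7–1.0 cm | 0.15–0.25 cm |

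**Formulas.** With equal numbers of boys and girls, the variance due to sex is d²/4. With visit ages spread evenly over W months within a centre, the variance due to age is r²W²/12. The removable share is s = (sex + age)/(SD² + sex + age). The detectable difference falls by 1 − √(1 − s). A comparison that had 80% power at two-sided 5% moves to Φ(2.80/√(1 − s) − 1.96). In cases (a) to (c) the low end pairs the smallest d and r with the largest SD, and the high end does the reverse.

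**Worked example, head circumference, sex only (W = 0).**

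- Low: 0.9²/4 = 0.2025; 1.6² = 2.56; s = 0.2025/2.7625 = 0.073; reduction 3.7%.
- High: 1.2²/4 = 0.36; 1.3² = 1.69; s = 0.36/2.05 = 0.176; reduction 9.2%.

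**Reduction in the detectable difference, all cases.**

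| Case | Weight | Length | Head circumference |
|---|---|---|---|
| (a) One visit age per centre, so only sex contributes | 1.6–4.7% | 1.0–3.4% | 3.7–9.2% |
| (b) Visits spread over 2 months within a centre, z-scores | 1.7–5.4% | 1.6–5.0% | 3.9–9.7% |
| (c) Upper bound: visits spread over 6 months with no centre pattern, z-scores | 3.2–10.8% | 6.4–15.6% | 4.9–13.1% |
| (d) Spread as in (c), but only a sex term added | 1.4–4.5% | 0.8–2.9% | 3.5–8.9% |

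For case (d), s = sex/(SD² + sex + age), taken as minimum and maximum over all combinations of the input limits.

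In case (a), 80% power becomes 81–84% for weight, 81–83% for length and 83–87% for head circumference.

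**Simulation of adding sex alone.** Head circumference at mid-range (d = 1.05 cm, SD 1.45 cm, 0.2 cm per month), with 300 children and 12 centres assumed, sandwich standard errors, 6000 runs, and no deaths or drop-out simulated. Power is for a 0.51 cm effect.

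| Visit pattern | Mean SE without / with sex | Rejection under no effect | Power |
|---|---|---|---|
| One fixed age per centre | 0.181 / 0.171 cm | 5.6% / 5.4% | 80.0% / 84.4% |
| Even over 6 months | 0.186 / 0.176 cm | 4.9% / 5.3% | 78.5% / 82.5% |

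**Second check on a different scale.** Here the sex difference and monthly growth are in units of the residual SD, visits are even over six months, and the model adds both sex and age (300 children, 10 centres, 2000 runs per scenario). The standard error fell by about 1% (sex difference 0.3, growth 0.05 per month), 5.6% (0.5 and 0.15) and 17% (0.9 and 0.3). In the middle scenario, power for a true effect of 0.30 rose from 68% to 73%, the mean estimate was 0.30 with and without the extra terms, and type I error was 4.4% both ways. When sex and age explained nothing, the standard error rose by about 0.4%, which is the price of being wrong.

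**The case against.** The strongest reply is that the outcome scale is simply not stated. A summary table in a condensed article may leave to the full protocol or SAP whether weight is analysed in kilograms or as a z-score. If z-scores for corrected age and sex are intended, GA and centre are enough and nothing remains. That stands as a condition on the point. It does not remove it, because the covariate set itself is stated twice, and on raw measurements it is the weaker choice.

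Second, adjusting for the stratification factors is a standard, uniform rule. The main model for the primary outcome also omits sex, which enters only an additional analysis, and weight and head circumference at hospital discharge follow the same GA-and-centre rule. This is fair: the omission is consistent policy and not a contradiction. The case for sex is that these outcomes are body size, where it predicts directly.

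Third, the gains are small at the low end, rest on assumed inputs, and affect three unpowered secondary outcomes. All true. For length, the gain from sex alone may be negligible.

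Fourth, the age part is the weakest. The article does not say that age or date at the visit is recorded, nothing in it supports an even six-month spread, and a z-score needs one growth reference for three countries. For that reason case (c) is an upper bound only, and the minimum fix does not depend on age.

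**Conclusion.** The point holds as a minor, nearly free gain in precision. If raw measurements are analysed as the article describes, sex variation, and age variation within centres, stays in the error term. Sex alone is worth a reduction in the detectable difference of roughly 1–5% for weight and length and 4–9% for head circumference (case a). Removing age as well adds between very little and, at most, enough to reach 10.8%, 15.6% and 13.1% for the three measures (case c). There is no added bias, no type I error problem and no effect on the primary outcome. The size rests wholly on assumed growth figures and on how visits are spread. Confidence is medium, because z-scores may already be intended.

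**What to change.** State that weight, length and head circumference at 18 to 24 months are analysed as z-scores for corrected age and sex from one named growth reference, in the same linear regression on treatment, GA and centre. This assumes that age or date at the visit is recorded.

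If it is not, or if raw scales are preferred, add sex as a covariate to the three regressions. Sex is a baseline variable already collected, so this needs no new data.

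Either version costs one sentence of analysis wording. If z-scores are already planned, naming the scale and the reference settles the matter.
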